# Intra-arterial versus standard intravenous administration of lutetium-177-DOTA-octreotate in patients with NET liver metastases: study protocol for a multicenter, randomized controlled trial (LUTIA trial)

**DOI:** 10.1186/s13063-019-3888-0

**Published:** 2020-02-05

**Keywords:** Intra-arterial, PRRT, NET, Neuroendocrine tumor, Neuroendocrine neoplasm, Lutetium-177-DOTATATE, ^177^Lu-DOTATATE

## Abstract

**Background:**

Lutetium-177-DOTA-octreotate (^177^Lu-DOTATATE) significantly increases survival and response rates in patients with grade I and grade II neuroendocrine tumors (NETs). However, survival and response rates are significantly lower in patients with bulky liver metastases. Increasing the tumor-absorbed dose in liver metastases may improve response to ^177^Lu-DOTATATE. The LUTIA (Lutetium Intra-Arterial) study aims to increase the tumor-absorbed dose in liver metastases by intra-arterial (IA) administration of ^177^Lu-DOTATATE, compared to conventional intravenous (IV) administration.

**Methods:**

A multicenter, within-patient randomized controlled trial (RCT) in 26 patients with progressive, liver-dominant, unresectable grade I or grade II NET will be conducted. Patients with bilobar bulky disease will be randomly allocated to receive IA treatment into either the left or the right hepatic artery. Using this approach, one liver lobe will be treated intra-arterially (first-pass effect), while the contralateral lobe will receive an intravenous treatment as a second-pass effect. The primary endpoint of this study is the difference in tumor-to-non-tumor ratio of ^177^Lu-DOTATATE uptake between the two liver lobes on post-treatment SPECT/CT (IA versus IV). Secondary endpoints include absorbed dose in both liver lobes, tumor response, dose-response relationship, toxicity, uptake in extrahepatic lesions, and renal uptake.

**Discussion:**

This multicenter, within-patient RCT will investigate whether IA administration of ^177^Lu-DOTATATE results in a higher activity concentration in liver metastases compared to IV administration.

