## Methods

### Hypothesis

The hypothesis is that IA administration of ^177^Lu-DOTATATE into the hepatic artery will result in a higher tumor-to-non-tumor (T/N) uptake ratio, compared to IV administration.

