#### Treatment

After providing informed consent, patients will be randomized to IA treatment of either the left or the right liver lobe. A complete treatment consists of four cycles of ^177^Lu-DOTATATE every 6 to 12 weeks [18]. On the day of treatment, patients will be hospitalized for one day and one night. Laboratory examination will be performed to ensure no toxicities have occurred and that the patient is fit for treatment and angiography. Prior to or at the start of the angiography procedure, co-infusion of amino acids (1 L 2.5% lysine/arginine during 4 h) is initiated and prophylactic oral anti-emetics (ondansetron 8 mg) are given. During the angiography, the allocated hepatic artery (i.e., left or right) will be catheterized via a femoral or radial approach. A nuclear medicine physician and interventional radiologist will determine the final injection position during angiography. In the first angiographic procedure, a cone-beam computed tomography (CBCT) scan will be performed with a catheter position identical to the injection position. The CBCT confirms the target tumor’s arterial blood supply and demonstrates the arteries’ perfusion territory. Next, 7400 MBq of ^177^Lu-DOTATATE is administered in 30 min, according to the instructions for use of Lutathera [19]. During every cycle, the same injection position is used (i.e., the same randomly allocated liver lobe is IA-treated four times).

All (serious) adverse events will be monitored and logged by medical personnel. A post-treatment ^177^Lu-DOTATATE SPECT/CT scan and total-body planar scintigraphy will be acquired 24 h (± 3 h) post-injection. The acquisition of the SPECT/CT scan after the first cycle is essential for the main study objective, while the SPECT/CT scans after the second, third, and fourth cycles will provide information on the secondary study objectives.

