### Objectives

The primary objective is to evaluate whether there is a difference in T/N activity concentration ratio on post-treatment SPECT/CT between the IA- and IV-treated liver lobes. As secondary objectives, activity concentration ratios and absolute mean values of tumor- and healthy liver-absorbed doses in the two lobes will be calculated and compared. Other secondary objectives include the post-treatment tumor response, dose-response relation, and post-treatment hepatic, hematologic, and renal toxicity. Activity concentration in contralateral liver tumors and extrahepatic tumor depositions and renal activity will also be assessed.

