### Outcome assessment

To determine the T/N activity ratio on post-treatment SPECT/CT, volumes of interest (VOIs) are drawn based on the pre-treatment contrast-enhanced CT or magnetic resonance imaging (MRI) scan. Only tumors with a minimal diameter of 3 cm are delineated, up to three tumors per liver lobe. For the normal liver tissue VOIs, a representative portion of the normal liver tissue is delineated in each liver lobe, with a minimal diameter of 3 cm. Of all delineated VOIs, the mean number of counts per voxel is calculated.

For the secondary endpoints, a dose-point kernel in commercially available software will be used to calculate the mean absorbed dose, based on the 24-h post-treatment SPECT/CT and mean effective half-life of ^177^Lu-DOTATATE [20, 21]. Comparisons are made between the IA and IV groups by means of a Student *t* test or Mann-Whitney *U* test, where appropriate. Tumor response is assessed on contrast-enhanced CT or MRI using the Southwest Oncology Group (SWOG) solid tumor response criteria, Response Evaluation Criteria In Solid Tumors version 1.1 (RECIST 1.1) and modified Response Evaluation Criteria in Solid Tumors (mRECIST) [22–24]. Response to treatment is assessed on both the patient and liver levels. Moreover, biochemical response will be evaluated using chromogranin A (CgA) levels, measured at baseline and during follow-up. Biochemical, hematological, and clinical toxicity will be graded according to the Common Toxicity Criteria on Adverse Events (CTCAE) version 4.03 [25].

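### The stated question is tumor activity, but the powered test is on the lobar T/N ratio; the tumor comparison needs a paired analysis and a role in the conclusion

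*Protocol article*

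**What the plan says.** The trial's purpose is described in terms of the tumor itself. The Abstract (Background) says that the "study aims to increase the tumor-absorbed dose in liver metastases by intra-arterial (IA) administration", and the Abstract (Discussion) says that the trial "will investigate whether IA administration of ^177^Lu-DOTATATE results in a higher activity concentration in liver metastases compared to IV administration". Trial design likewise describes comparing tumor activity between the IA-treated lobe and the other lobe. The end of the main Discussion links higher tumor activity to better response and survival, and says that positive results will lead to a large trial.

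The formal plan is written in terms of T/N:
- Abstract, Methods: "The primary endpoint of this study is the difference in tumor-to-non-tumor ratio of ^177^Lu-DOTATATE uptake between the two liver lobes on post-treatment SPECT/CT".
- Hypothesis: IA administration "will result in a higher tumor-to-non-tumor (T/N) uptake ratio, compared to IV administration".
- Objectives: "The primary objective is to evaluate whether there is a difference in T/N activity concentration ratio on post-treatment SPECT/CT".
- Sample size assessment and Statistical analysis: a paired t test on the T/N ratio.

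On the denominator, Outcome assessment says that "a representative portion of the normal liver tissue is delineated in each liver lobe, with a minimal diameter of 3 cm". On delivery, Treatment says that "the allocated hepatic artery (i.e., left or right) will be catheterized via a femoral or radial approach".

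Absolute absorbed doses in tumor and healthy liver are compared between lobes as a secondary objective. Outcome assessment assigns that comparison a Student t test or a Mann-Whitney U test between the IA and IV groups.

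**The concern.** A T/N ratio answers whether IA delivery favors tumor over normal liver. The question in the Abstract is whether tumor receives more. The two coincide only if normal liver in the infused lobe is unaffected by the infusion, and the article nowhere says that it is. Catheterizing a left or right hepatic artery plausibly exposes the parenchyma in that territory to the first pass as well, so treatment may change the denominator in that lobe.

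Two things are at stake. A real tumor gain that normal liver partly shares could give a null primary result, or a stop at the futility look after ten patients. And a positive T/N result would not, by itself, support a statement that tumor concentration rose. The analysis that would support it is planned, but it is not tied to the conclusion. It is also given tests that do not fit lobes paired within a patient.

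**Working it through.** **1. The plan's own figure.** Inputs from Sample size assessment: dz = 0.65 on the within-patient T/N difference, one-sided α = 0.025, looks at n = 10 and n = 26, boundaries T1 = −0.1045056 and T2 = 2.045732.
- Fixed paired t test: df = 25, noncentrality 0.65 × √26 = 3.31, power 0.890.
- Two-look design, 1,000,000 simulated trials: power 0.888, one-sided type I error 0.025.

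The stated power of about 0.9 reproduces. It applies to an effect of 0.65 SD on T/N and says nothing about tumor counts.

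**2. What T/N measures.** Let IA multiply tumor uptake by a and same-lobe normal-liver uptake by b, relative to the contralateral lobe. Then

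log(T/N ratio, IA over IV) = log(T_IA/T_IV) − log(N_IA/N_IV) = log a − log b.

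On the planned difference scale, with contralateral T/N equal to r, the difference is r(a/b − 1), which is zero whenever a = b. This takes T and N from the same lobe, which is inferred from the endpoint definition and the outlining rule. All b values below are assumed. The 2.4 is the article's cited maximum tumor-fold increase, from three patients given another radiopharmaceutical.

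| a (tumor) | b (normal liver) | T/N ratio, IA over IV |
|---|---|---|
| 1.5 | 1.5 | 1.00 |
| 2.4 | 1.0 | 2.40 |
| 2.4 | 1.5 | 1.60 |
| 2.4 | 2.4 | 1.00 |
| 1.5 | 2.0 | 0.75 |

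In the first row tumor concentration is up by 50% and T/N does not move. The cited 3.75-fold and 2.4-fold gains are both on tumor uptake, not on T/N.

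**3. Effect on power.** Assume that the tumor effect alone is dz = 0.65, that the SD is unchanged, and that normal liver shares a fraction f of the effect on the log scale. The T/N effect is then 0.65 × (1 − f).

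| f | dz on T/N | Power at n = 26 (fixed t) |
|---|---|---|
| 0 | 0.65 | 0.89 |
| 0.25 | 0.4875 | 0.67 |
| 0.50 | 0.325 | 0.36 |
| 0.75 | 0.1625 | 0.12 |
| 1 | 0 | 0.025 |

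The two-look design gives the same values to within 0.003. In the simulation the n = 10 futility boundary is crossed in 1.5% of trials when dz on T/N is 0.65 and in 46% when it is 0, which is the fully shared case.

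**4. The tests for the tumor comparison.** Both lobes come from the same patient and the same scan. If lobe values have equal SD σ and within-patient correlation ρ, the paired standard error is σ√(2(1 − ρ)/n). Treating the lobes as independent groups gives σ√(2/n). The paired error is smaller by the factor √(1 − ρ) whenever ρ is positive. The main Discussion itself credits the paired design with a gain in power. Mann-Whitney U is a test for independent samples, and a Student t test between groups reads the same way.

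**The case against.** T/N is a deliberate and consistent choice. Hypothesis, objective, endpoint, sample size and analysis all use it, and the main Discussion sets clinical relevance on the same scale. Selectivity matters when hepatic toxicity is an objective, so an equal rise in tumor and normal liver is not clearly a benefit missed. T/N also has a technical merit: if IA-treated tumors deplete what reaches the other lobe, tumor and normal liver there may fall together, and the ratio largely cancels this. The lobe-level doses are already planned and would expose a shared rise. Ranking of secondary endpoints may sit in an analysis plan that is not shown. All of this stands, and it is why T/N should stay primary.

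It does not settle two things that the article itself states: a question about tumor concentration that the powered test does not answer, and independent-group tests for the comparison that would answer it.

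A reader might go further and infer that T/N could as easily mimic an effect. For example, a = 1.0 and b = 0.8 gives 1.0/0.8 = 1.25 with no tumor gain. The article gives no reason to expect lower normal-liver uptake in the infused lobe. Because the side is randomized, stable left-right differences add noise and do not systematically favor IA. Nor is normal liver IA-exposed in both lobes: only one lobe is infused. Finally, the article does not say that a T/N result alone will be reported as higher tumor concentration or will trigger the large trial.

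**Conclusion.** The point holds as a mismatch between the stated question and the powered test, not as a flaw in choosing T/N. A T/N difference alone shows selectivity. A tumor gain shared by normal liver is diluted, and under the assumptions above power falls to 0.67 if a quarter of it is shared and to 0.36 if half is. These sizes rest on an assumed tumor effect of 0.65, an unchanged SD and assumed shares. The article gives neither a normal-liver multiplier nor a baseline T/N, so the true dilution could be anywhere from none to complete. That the first pass raises normal liver in the infused lobe is an inference from catheter placement and the outlining rule. The mismatch in test type does not depend on any of these assumptions.

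**What to change.** - Keep T/N as the primary endpoint and describe it as a measure of selectivity.
- Make the cycle-1 within-patient ratio of mean tumor counts, IA lobe over IV lobe, the first-ranked secondary endpoint. Analyze it as paired data, for example the mean log ratio with a 95% CI, back-transformed. Report the matching normal-liver ratio beside it.
- In Outcome assessment, replace the Student t and Mann-Whitney U tests with paired methods for all lobe comparisons.
- State the conclusion rule: higher tumor activity concentration is claimed only if the CI for the tumor ratio lies above 1. A T/N difference alone is reported as higher selectivity.

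The cost is wording, since the same scan and the same outlined volumes supply the measure. There are two downsides. The headline claim then depends on a second result that is not formally powered. The raw tumor ratio also leans more heavily than T/N on the main Discussion's assumption that depletion of activity reaching the other lobe is negligible. If the sponsor prefers not to add the rule, the minimum is to reword the Abstract and the closing Discussion so that the stated question is T/N selectivity.

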**Trial registration:**

ClinicalTrials.gov, NCT03590119. Registered on 17 July 2018.

## Background

Peptide receptor radionuclide therapy (PRRT) with lutetium-177-DOTA-octreotate (^177^Lu-DOTATATE; Lutathera, Advanced Accelerator Applications, Saint-Genis-Pouilly, France) is the standard treatment for inoperable metastasized grade I and grade II gastrointestinal neuroendocrine tumors (NETs) [1]. Grade I and grade II NETs are well or moderately differentiated tumors. However, metastatic disease at initial diagnosis is present in approximately 50% of patients [2, 3]. The liver is the most frequently affected site of metastases, followed by the peritoneum, bone, lung, and ovary [4]. In order to control disease progression, to achieve symptomatic relief, and to prolong survival, PRRT is increasingly used in the treatment of progressive NETs [5, 6]. ^177^Lu-DOTATATE is a radiopharmaceutical, consisting of a somatostatin-analog peptide labeled with an isotope with a high-energy beta emission, that binds with high affinity to the somatostatin receptor subtype 2 (SSTR-2), overexpressed in grade I and II NET cells [7, 8]. ^177^Lu-DOTATATE significantly increases progression-free survival (PFS) and overall survival (OS), with limited toxicity, compared to non-radioactive high-dose somatostatin analogs in patients with advanced stage NET [5, 6, 9–11].

However, patients with liver metastases have a significantly lower PFS, even after ^177^Lu-DOTATATE treatment [12, 13]. A post hoc analysis of the NETTER-1 trial showed that the presence of bulky lesions (> 3 cm) was significantly associated with a worse PFS after PRRT [14].

To improve the absorption and binding of the radiopharmaceutical to NET cells, small studies have evaluated the effect of intra-arterial (IA) administration of several different radiopharmaceuticals (e.g., ^177^Lu-DOTATATE, ^90^Y-DOTATOC, etc.) into the common hepatic artery [15]. Tumor-absorbed doses seemed to be higher after IA administration of the radiopharmaceutical, but comparative studies have not been performed [15].

The current study compares IA administration of ^177^Lu-DOTATATE with intravenous (IV) administration. This manuscript provides a detailed description of the study protocol.

## Methods

### Hypothesis

The hypothesis is that IA administration of ^177^Lu-DOTATATE into the hepatic artery will result in a higher tumor-to-non-tumor (T/N) uptake ratio, compared to IV administration.

### Trial design

The Lutetium Intra-Arterial (LUTIA) study is a multicenter, open-label, phase II, within-patient RCT. The study design differs from the standard parallel-group design, in which patients are allocated by randomization to either the treatment or the control group [16]. Instead, patients will act as their own control, by treating only half of the liver by IA administration of ^177^Lu-DOTATATE. Via the systemic circulation, the contralateral lobe and extrahepatic disease will be treated as if by IV administration (second-pass effect; see Fig. 1). ^177^Lu-DOTATATE activity in tumors in the IA-treated lobe will be compared with the activity in tumors in the contralateral lobe (IV-treated).

**Fig. 1 Fig1:**
[figure not shown]
Treatment principle. **a** IA administration of ^177^Lu-DOTATATE selectively in the right or left hepatic artery (right in this figure). **b** Systemic circulation of ^177^Lu-DOTATATE after IA administration. **c** Treatment of whole liver (second-pass) and other organs

The study will be conducted in accordance with the Declaration of Helsinki and current guidelines of Good Clinical Practice. The current research protocol has been approved by the central Research Ethics Committee of the University Medical Center Utrecht (reference approval number 17-446), and we will not begin recruiting at other centers in the trial until local ethical approval has been obtained. The study protocol has also been approved by the radiation protection committees of the participating centers (i.e., University Medical Center Utrecht, Erasmus Medical Center Rotterdam, Antoni van Leeuwenhoek Amsterdam). A Standard Protocol Items: Recommendations for Interventional Trials (SPIRIT) checklist is provided in Additional file 1. Figure 2 shows the schedule of interventions and assessments [17].

**Fig. 2 Fig2:**
[figure not shown]
SPIRIT figure showing all phases of the trial, including the interventions and assessment time points

### Subjects

All patients with World Health Organization (WHO) grade I or II NET, originating from gastric, enteric, or pancreatic origin with hepatic metastases and an indication for PRRT are eligible for inclusion. The total hepatic burden should be estimated to involve at least 25% of the liver volume, with a minimum of one lesion of at least 3 cm in size in each liver lobe on cross-sectional imaging. A size of at least 3 cm is required for reliable measurement of activity on single photon emission computed tomography (SPECT)/computed tomography (CT).

### Recruitment

Patients will be recruited in three centers (European Neuroendocrine Tumor Society [ENETS] Centers of Excellence) in The Netherlands. During a multidisciplinary tumor board, patients will be reviewed for eligibility to participate in the study. Study information will be provided by the study physician, nuclear medicine physician, or oncologist/endocrinologist. General inclusion and exclusion criteria for PRRT, as described in the ENETS guidelines, will be applied (Table 1) [1, 18].

**Table 1 Tab1:** Detailed inclusion and exclusion criteria

Inclusion criteria	Exclusion criteria
Patients must have given written informed consent	Any previous radioembolization, chemoembolization, bland embolization, or external beam radiation therapy to the liver, at any time, or surgery or radiofrequency ablation (or other ablative therapies) within 12 weeks prior to randomization in the study
Male or female aged 18 years or older	Interferons, everolimus (mTOR-inhibitors), or other systemic therapies within 4 weeks prior to randomization in the study
Inoperable histologically proven neuroendocrine tumor with an indication for ^177^Lu-DOTATATE	Use of octreotide or octreotide LAR, if it cannot be interrupted for 24 h or 4 weeks before therapy, respectively, unless tumor uptake on somatostatin receptor imaging is higher than normal liver uptake
Ki-67 index ≤ 20% and a mitotic count of ≤ 20	Unresolved toxicity from previous anti-cancer therapy greater than grade 2
Confirmed presence of somatostatin receptors on target lesions	Serum bilirubin > upper limit of normal (ULN), serum albumin < 3.0 g/dL
Life expectancy of 6 months or longer	Glomerular filtration rate < 50 ml/min
Eastern Cooperative Oncology Group (ECOG) performance score 0–1	Hb < 5.5 mmol/L; leucocytes < 3.0 × 10^9^/L; platelets < 100 × 10^9^/L (at baseline; 75 × 10^9^/L is sufficient for cycles 2–4)
At least one lesion ≥ 3 cm on cross-sectional imaging in both the right and left liver lobes	Uncontrolled congestive heart failure or diabetes mellitus
Presence of excessive liver metastases, defined as > 25% tumor burden	Patients suffering from diseases with an increased chance of liver toxicity
Patients must have clinical or radiological progressive disease	Patients declared incompetent or suffering from psychic disorders making comprehensive judgement impossible
Negative pregnancy test for women of childbearing potential	Previous enrollment in the present study or previous treatment with ^177^Lu-DOTATATE
	Female patients who are not using an acceptable method of contraception, OR are less than 1 year postmenopausal or surgically sterile
	Male patients who are not surgically sterile or do not use an acceptable method of contraception
	Body weight more than 150 kg
	Current spontaneous urinary incontinence
	Severe allergy for intravenous contrast

### Study procedures

#### Screening

At baseline, demographic data, medical history, medication usage, current complaints, physical examination, and WHO performance status will be recorded (Fig. 3). Furthermore, patients will undergo the following investigations: ^68^Ga-labeled somatostatin analog positron emission tomography/computed tomography (^68^Ga-SSTR PET/CT) to ascertain sufficient somatostatin receptor expression; contrast-enhanced diagnostic CT of the liver to acquire hepatic tumor size and location; laboratory investigations to assess the general condition and presence of toxicity (i.e., liver enzyme and bilirubin levels, coagulation tests, kidney function, and hematologic tests).

